### Study procedure

All enrolled women are observed from their first visit after positive pregnancy test (OTTILIA) or before commencing a new ART cycle (FIRST) until the end of pregnancy or ART procedure (negative pregnancy test/end of pregnancy, if successful cycle), respectively.

At baseline, clinical information and index- pregnancy/ART cycle details are obtained from all women by a specially trained staff (Table 2). Data are collected by means of questionnaires and recorded in a web-based database including an electronic form for each woman enrolled. To ensure high quality data, a centralized data management performs quality control and plausibility checks according to predefined procedures. Follow-up data (Table 2) are collected during the three trimesters of pregnancy and in the puerperium period (6 weeks after delivery), at the time of hospital stay, routine clinical follow-up visits or telephone interviews.

**Table 2 Tab2:** Baseline and Follow-up data for evaluation and monitoring of women enrolled in the OTTILIA and FIRST registries

OTTILIA	
Baseline Clinical information: • Maternal age • Body Mass Index • Smoking habit • Reproductive history (previous pregnancies and obstetric complications occurred) • Personal and family history of VTE • Presence of inherited or acquired thrombophilias • Thrombophilic risk factors Index-pregnancy information: • Results of performed imaging tests, (ultrasonography, Doppler ultrasonography) • Invasive prenatal testing (i.e. villous sampling, amniocentesis) • Antithrombotic prophylaxis (brand, doses/day, duration)	Follow-up Pregnancy outcomes: • Live birth (gestational age, delivery mode, sex, birth weight, fetal or maternal hemorrhage) • Obstetric complications (PL, IUFD, gestational hypertension, preeclampsia, HELLP syndrome, SGA newborns, placental abruption) • VTE
FIRST	

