### Statistical analysis plan

Absolute numbers, percentage and median (range) or mean (±standard deviation) will be calculated to describe study groups and sub-groups. Associations between aforementioned primary and secondary outcomes and both numerical and categorical variables (age, drugs, co-morbidities, medical procedures, drug regimens and doses, etc.) collected during study will be tested. Relative risk value, with a 95% confidence interval, will be computed for the comparison of outcomes occurrence.

Validity of primary results will be examined, using a sensitivity analysis of sub-groups and applying more than one statistical test. Parametric and non-parametric statistical tests, according to data distributions, will be used for comparison of categorical and numerical variables. Strategy to prevent missing data will be employed. We select clinical information and laboratory measurements that are routinely included in the ‘real word’ practice, to facilitate the adherence of the investigators to the study protocol. Contacts will be kept with the investigators to reduce the burden of missing data as much as possible. A query-based system will allow us to ask investigators for the missing variables, whether the variables are meaningful for the final analysis. A *p* value below 0.05 will be considered to define statistical significance.

Stratification according to sub-groups of subjects will be taken into account on the basis of propensity to receive or not the treatment. This strategy will allow for an accurate and statistically valid analysis of heterogeneity that will be eventually observed. Potential confounding factors will be identified and after the evaluation of possible relationship between single variables by univariate analysis, logistic regression analysis will be performed to estimate the independence of associations identified. Data analysis will be performed also taking into account type of molecules administered, starting time and duration of thromboprohylaxis.

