### Study size estimation

In the literature, the likelihood of observing live births without any treatment is estimated to range between 55 and 80% [2]; a multicentre Italian study [9] showed the occurrence of complications in 50% of all untreated women during pregnancy. Given these estimates, for the OTTILIA register, in order to observe an absolute increase of 15–20% (statistical power: 80%, significance level: 0.05), we calculated the inclusion of 190–340 thrombophilic women and, simultaneously, a cohort of pregnant women with the same clinical history (see inclusion criteria) not carrying inherited thrombophilia, in a ratio of at least 1:1. Thus, an overall number of 380–680 consecutive pregnancies are needed.

As far as the FIRST register is concerned, we estimated the inclusion of 624 women. This estimate is calculated on the basis of (1) the probability of observing live births after ART procedures (20–30%), (2) the estimate of an absolute increase of 5–10% in the number of live births after a prophylaxis of LMWHs (statistical power: 80%, significance level: 0.05).

It has been estimated that the OTTILIA and FIRST registries will be executed in the periods February 2012–December 2020 and October 2015–September 2020, respectively. In both the registries, an additional period of 9 months from the date of the last enrollment will be considered.

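### LMWH duration and starting time are to be related to outcome with no method that aligns exposure with the start of follow-up; duration is biased by construction, and ever/never LMWH is biased wherever treatment starts after entry

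*Protocol article*

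**What the plan says.** Protocol article, Study procedure: "All enrolled women are observed from their first visit after positive pregnancy test (OTTILIA) or before commencing a new ART cycle (FIRST"), so the clock starts at the first visit in one registry and before the cycle in the other. Under Design and setting, LMWH is not assigned in advance but follows local practice.

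Table 2 records "Antithrombotic prophylaxis (brand, doses/day, duration") in the baseline column of both registries. That column also holds items that arise after entry: amniocentesis and villous sampling in OTTILIA, oocytes retrieved and embryo transfers in FIRST.

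Statistical analysis plan: outcomes are tested against drugs, regimens and doses collected during the study. The tools are relative risks with 95% confidence intervals, parametric and non-parametric tests, stratification by propensity to be treated, and logistic regression. The section closes with: "Data analysis will be performed also taking into account type of molecules administered, starting time and duration of thromboprohylaxis". It names no exposure time zero, landmark, time-dependent exposure or time-to-event method.

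Study size estimation gives the effects sought: 15–20 points in OTTILIA and 5–10 points in live births after LMWH in FIRST. A possible benefit of LMWH is part of primary aim 2.

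**The concern.** Three quantities are at issue.

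- **Total duration.** A loss or a negative test normally ends prophylaxis, so short duration is often the result of failure. Relating duration to live birth then measures the outcome against itself. This needs no assumption about late starts.
- **Ever versus never LMWH.** If some women start after entry, those who fail before their start would fall among the untreated in a simple comparison. The treated group is then selected for having survived to the start.
- **Starting time among the treated.** A woman who starts late must still have been pregnant, or in cycle, at that point. Unaligned, late start is favoured for the same reason.

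Propensity stratification balances the factors behind the decision to treat. It does not return women who failed before starting to the group they were meant for. At stake is the reading of primary aim 2, and in FIRST the contrast on which the sample size rests.

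**Working it through.** **1. The plan's own figures, as a benchmark.** Inputs: "statistical power: 80%, significance level: 0.05" (sidedness not stated; two-sided taken), "in order to observe an absolute increase of 15–20" per cent, and a 50% base rate as in the cited Italian study, which "showed the occurrence of complications in 50% of all untreated women during pregnancy". Per group:

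n = [1.960·√(2p̄(1−p̄)) + 0.842·√(p₁(1−p₁)+p₂(1−p₂))]² / (p₂−p₁)²

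- 50% to 65%: (1.370+0.582)²/0.0225 = 169.3, so 170 per group and 340 in total.
- 50% to 70%: (1.358+0.571)²/0.04 = 93.0, so 93 per group and 186 in total.
- The article: "we calculated the inclusion of 190–340 thrombophilic women". The upper end matches exactly and the lower end is within 3%.
- FIRST, 20% to 30% with continuity correction: 313 per group, 626 in total, against 624 stated.

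The stated numbers fit a two-group comparison at these differences, so 15–20 and 5–10 points are the right yardsticks for a bias.

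**2. Duration, with no true effect.** Assumptions: every woman starts at enrolment and continues to loss or delivery; 70% live birth (inside the article's range: "the likelihood of observing live births without any treatment is estimated to range between 55 and 80" per cent); loss times exponential with mean 4 weeks after enrolment.

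- Under 20 weeks of LMWH: only losses, so 0% live birth.
- 20 weeks or more: 0.70/(0.70 + 0.30·e⁻⁵) = 0.70/0.7020 = 99.7%.

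Women who stop early for other reasons would soften this contrast but not remove it.

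**3. Ever versus never LMWH, with no true effect.** Let p = live-birth rate, q = share intended for LMWH, x = share of pregnancies or cycles that end before the planned start.

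- Treated: p/(1−x). Untreated: p(1−q)/[(1−q)+qx].
- With q = 0.5 the difference is 2px/(1−x²).

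FIRST, p = 25% (middle of the article's 20–30%), q = 0.5 assumed:

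| x | Treated | Untreated | Difference |
|---|---|---|---|
| 2% | 25.5% | 24.5% | 1.0 |
| 5% | 26.3% | 23.8% | 2.5 |
| 10% | 27.8% | 22.7% | 5.1 |
| 15% | 29.4% | 21.7% | 7.7 |

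For scale, at x = 10% and N = 624 the groups are 624×0.5×0.9 = 281 treated and 343 untreated. The standard error is √(0.2778×0.7222/281 + 0.2273×0.7727/343) = 0.035, so z = 0.0505/0.035 = 1.44. A nominal 5% test then rejects about 30% of the time, since Φ(1.44−1.96) ≈ 0.30.

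OTTILIA, p = 70%, q = 0.5 assumed, f = share of losses that precede the planned start, x = (1−p)f:

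| f | Treated | Untreated | Difference |
|---|---|---|---|
| 0% | 70.0% | 70.0% | 0 |
| 10% | 72.2% | 68.0% | 4.2 |
| 20% | 74.5% | 66.0% | 8.4 |
| 30% | 76.9% | 64.2% | 12.7 |
| 40% | 79.5% | 62.5% | 17.0 |
| 50% | 82.4% | 60.9% | 21.5 |

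Over p = 55–80% and q = 0.3–0.7, f = 10% gives 2 to 8 points. Reaching 15 points needs 20–61% of losses before the start, and reaching 20 points needs 27–79%.

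**4. The net direction is not fixed.** Assume 65% live birth, 80% of losses spread evenly over weeks 5–12, and no effect. Losses are then 0.35×0.80/7 = 4 points per week. If treated women enter and start at week 5 while untreated women enter at week 8, the untreated have already been selected for three weeks of survival: 0.65/(1−0.12) = 74%, against 65% treated. That is about 9 points against LMWH.

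**5. After alignment.** Classifying exposure at a common time zero gives a simulated null difference of −0.001 to 0.000 at p = 55%, 65% and 80%. The stated sample sizes do not change.

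**The case against.** The strongest reply is that the article says only that timing will be taken into account. It does not state that starting time or duration enters a model as a fixed covariate, nor that women who fail before starting count as untreated. The article condenses a fuller plan that may define exposure. This stands as a limit: the fixed-covariate reading is an inference from the methods named. It does not rescue duration, because none of those methods can use total duration without the problem shown in step 2.

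Second, late start in OTTILIA is not documented. Prophylaxis sits in the baseline column and could begin at the first visit, in which case the ever/never bias is zero. This stands. The column heading settles little either way, since the same column holds procedures done after entry and duration cannot be known at entry. FIRST is the more plausible case because women enter before the cycle, but no start times are given there either.

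Third, a reader might infer that immortal time alone delivers the 15–20 or 5–10 points sought, or that an ineffective treatment would look effective in both registries. The article does not support this. The size depends on start times and timing of losses that it does not report, and step 4 shows that differential late entry can push the other way. Confounding by indication may do so too.

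Fourth, Table 2 lists neither gestational week at enrolment nor LMWH start dates, and a reader might conclude that they are not collected. That does not follow: the table is a summary, and the plan to use starting time implies that it is recorded.

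Last, the Discussion expects variable adherence, so the 0% versus 99.7% contrast is an extreme. Agreed; the defect remains in milder form.

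**Conclusion.** The point holds in two parts of unequal strength.

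- **Duration (firm).** Used as a predictor of live birth or clinical pregnancy, total LMWH duration will show an association with no true effect. This rests only on losses and failed cycles normally ending treatment.
- **Ever/never LMWH (conditional).** Where treatment starts after entry, immortal time favours LMWH. With no true effect the bias is 0 to over 20 points in OTTILIA, and 0 if all start at entry. In FIRST it is about 1 to 7.7 points for 2–15% of cycles stopping before the start, at 25% live birth with half intended for LMWH. The FIRST range overlaps the 5–10 points sought. In OTTILIA, 15–20 points is possible but needs a large share of losses before the start.

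These sizes are for the immortal-time component only. The net bias in either registry cannot be signed or sized from the article.

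**What to change.** In the Statistical analysis plan section:

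1. State that total LMWH duration will not be used as a predictor of live birth or clinical pregnancy.
2. Define exposure at a common time zero. Either use a landmark (a fixed gestational week in OTTILIA, a fixed point in the cycle in FIRST) among pregnancies or cycles still ongoing, or treat LMWH as a time-dependent exposure on gestational age with delayed entry at enrolment.
3. Analyse starting time only within that framework.
4. Confirm that gestational week at enrolment and LMWH start and stop dates are captured.

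The cost is mainly analysis work, and the planned numbers stay as they are. If a date proves not to have been captured, it would have to be retrieved for women already enrolled, given planned recruitment from 2012 (OTTILIA) and 2015 (FIRST); the query system described in the plan could serve. A landmark analysis has a price: it leaves out early losses or cycles that never reach the landmark, so it answers a question about a narrower population, and it counts later starters as untreated at the landmark. Reporting more than one landmark would show how much this matters.

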### Design and setting of the study

OTTILIA and FIRST registries are two prospective, studies designed to investigate pregnancy or ART outcomes according to different clinical and laboratory features and clinical management in women consecutively observed because of previous reproductive failures after spontaneous or assisted conception, respectively.

The possible assignment of women to treatments (such as LMWH) is not decided in advance but instead falls within current practice.

Obstetrics and Gynecology Departments as well as Thrombosis Centers with local Ethical Committee approval are allowed to participate to these studies.

Authors adhered to SPIRIT guidelines.

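### Starting time and duration of LMWH are to be analysed with methods that have no time axis, which biases the results toward longer or later LMWH even if it has no effect

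*Protocol article*

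**What the plan says.** The Statistical analysis plan section of the protocol article names its association methods. For effect size: "Relative risk value, with a 95% confidence interval, will be computed for the comparison of outcomes occurrence". For adjustment: "logistic regression analysis will be performed to estimate the independence of associations identified". For treatment selection: "Stratification according to sub-groups of subjects will be taken into account on the basis of propensity to receive or not the treatment". It closes with the commitment at issue: "Data analysis will be performed also taking into account type of molecules administered, starting time and duration of thromboprohylaxis".

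Three other places set the time structure:

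- Design and setting of the study: assignment to treatments such as LMWH "is not decided in advance but instead falls within current practice". LMWH may therefore begin at any time after entry.
- Study procedure: observation begins at the first visit after a positive test in OTTILIA, or before a new cycle in FIRST, and runs "until the end of pregnancy or ART procedure (negative pregnancy test/end of pregnancy, if successful cycle), respectively".
- Table 2: antithrombotic prophylaxis appears in the Baseline column, described by brand, daily doses and duration. No start date is listed. The Discussion counts recording how long women are treated among the registries' merits, which points to actual rather than planned duration.

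**The concern.** Realised duration is known only once the outcome is known. LMWH given for a pregnancy or cycle cannot run on after it has failed, so short duration is partly a result of failure. Starting time has the mirror problem. A woman who starts at week 10, or at embryo transfer, has already passed the period in which many failures occur, while a woman who failed earlier can only count as untreated or as an early starter.

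A relative risk or logistic model on the final outcome cannot tell these effects from a treatment effect. Propensity strata and baseline covariates deal with who is chosen for treatment, not with surviving long enough to receive it. Perfect start and stop dates would not help if the analysis ignores time.

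The primary aims include the potential benefit of LMWH and the profile of women who may benefit, and the article says the results should support clinical decisions. An artefact in the timing and duration results would bear directly on that use.

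**Working it through.** **The plan's own figures.** None is given for the timing or duration analysis. The benchmark is the planned effect in Study size estimation: 15–20 points in OTTILIA and 5–10 points in FIRST, at 80% power and 0.05. The sizes reproduce with a two-sided test and 1:1 groups. For OTTILIA, 50% v 65% gives 2 × 170 = 340, and 50% v 70% gives 2 × 93 = 186 (stated: 190). For FIRST, 20% v 30% with continuity correction gives 2 × 313 = 626 (stated: 624). The point does not rest on these sizes.

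**Null model for OTTILIA (assumed, not in the document).** LMWH has no effect. The weekly loss hazard is 5% in weeks 6–11, 1.2% in weeks 12–19 and 0.2% in weeks 20–37.

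- Live birth L = 0.95^6 × 0.988^8 × 0.998^18 = 0.735 × 0.908 × 0.965 = 64.4%. This lies within the 55–80% that the article cites for untreated women.

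**Duration, all starting at week 6.**

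- Twelve or more weeks of LMWH requires reaching week 18: S(18) = 0.735 × 0.988^6 = 0.684.
- Live birth with 12 or more weeks: 0.644 / 0.684 = 94%. With fewer than 12 weeks, every woman has lost the pregnancy: 0%.

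**Starting time.** Live birth among starters is L divided by the mean survival to the start week.

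- Starts at weeks 6–7: 0.644 / 0.975 = 66%.
- Starts at weeks 10–12: 0.644 / 0.774 = 83%.

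**Ever v never treated by hindsight, half intended for LMWH.** Let m be the mean survival to the intended start. Ever treated = L / m. Never treated = L / (2 − m), because women who fail before starting join the never group.

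| Start window | m | Ever | Never | False difference |
|---|---|---|---|---|
| At entry (week 6) | 1.000 | 64.4% | 64.4% | 0 |
| Weeks 6–7 | 0.975 | 66.0% | 62.8% | 3.2 points |
| Weeks 6–8 | 0.951 | 67.7% | 61.4% | 6.3 points |
| Weeks 6–12 | 0.862 | 74.7% | 56.6% | 18.1 points |

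If 80% are intended for LMWH, never = 0.2L / (0.2 + 0.8(1 − m)), and the last three rows become about 7.5, 14 and 33 points.

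**FIRST (assumed).** A positive test follows 40% of transfers and live birth 73.5% of positives, so live birth per transfer is 0.40 × 0.735 = 29.4%. Half intend LMWH from transfer, and a fraction f of cycles has no transfer. Never treated = 29.4% × (1 − f) / (1 + f).

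- f = 15%: 29.4% v 21.7%, a false 7.7 points.
- f = 5%: 29.4% v 26.6%, a false 2.8 points.
- LMWH from cycle start: 0.

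**Does adjustment help?** A second null simulation used exponential time to loss (mean 3 or 8 weeks), base live birth of 55% or 80%, starts from week 5 to week 6, 8 or 12, and a baseline confounder correctly entered in the logistic model. The adjusted odds ratio was still 1.12–1.46 per week of later start and 1.14–5.06 for ever v never. With the confounder left out, the crude ever/never relative risk was 0.93–1.01 in the earliest-start scenarios.

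**Does a landmark help?** Among women still pregnant at week 13, live birth is 0.644 / 0.726 = 88.6% whatever the exposure, which is the correct null. But (1 − 0.726) / (1 − 0.644) = 77% of losses occur before that landmark and are excluded.

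**The case against.** The strongest reply is that the error is inferred. The closing sentence says only that timing and duration will be taken into account. It does not say that total duration will predict live birth, and it could cover description, or analysis of bleeding and thrombosis. Time zero and exposure coding are often left to a fuller plan. It is true that linking timing to relative risk and logistic regression is a reading. But the article commits to the analysis and names its association methods, and none handles time. The point is about a stated choice, not an omitted detail.

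Second, a reader might infer that the registries will show a false benefit as large as the planned effect, and that the aims on LMWH will be answered wrongly. The document does not support that. The 18-point and 8-point figures come from an ever/never contrast that the timing sentence does not mention. They also need LMWH to start well after entry and to be classed by hindsight. No start times are given, and with start at entry or at cycle start the difference is zero.

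Third, it is tempting to say that LMWH will look protective. That is only the direction of this bias. Confounding by indication can offset it, as the crude ratios of 0.93–1.01 show.

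Fourth, Table 2 places duration under Baseline. If planned duration at entry were analysed, the truncation would not apply. The layout does not settle this, since invasive prenatal testing is in the same column and the Discussion's wording suggests actual duration. The ambiguity stands and needs an answer.

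**Conclusion.** The concern holds for the analyses of starting time and duration. Carried out with the named methods, they are biased toward longer or later LMWH appearing beneficial when it has no effect, and propensity or baseline adjustment does not remove this.

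The duration artefact is near-total (94% v 0%) and does not depend on spread-out starts. It does require that realised duration is used. For hindsight ever/never classification the size is conditional: 0, about 3, about 6 or 18 points in OTTILIA as the start window widens from entry to weeks 6–12 with half intended for treatment, and 0, about 3 or about 8 points in FIRST. All of these rest on assumed loss hazards, start times and transfer rates. The net direction in the real data is not certain, and the main treated/untreated comparison is affected only if LMWH often starts after entry and is classed by what happened later.

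**What to change.** Amend the analysis wording as follows:

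- State that realised total duration is descriptive only and is not a predictor of live birth or clinical pregnancy.
- Fix a time zero: the first visit in OTTILIA; in FIRST, cycle start, or transfer among women who reach transfer.
- For the main comparison, classify LMWH by status at time zero.
- Model later starts and stops as a time-varying exposure on the gestational or cycle time scale.
- Use landmark analyses only as a supplement, at early or several landmarks, and state that losses before each landmark are excluded.
- Say whether the duration listed under Baseline in Table 2 is planned or actual, and confirm that start and stop dates are recorded.

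The cost is wording and programming, plus data queries if dates were not captured. Women who start after time zero count as untreated in the main comparison, which dilutes that contrast. The time-varying model removes the survival artefact but not confounding by the reasons for starting or stopping.
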